**Fig. 1 Fig1:**
[figure not shown]
Schema for an individually-randomized controlled trial of the IMARA-SA intervention

### Randomization

We will use a 1:1 randomization allocation to assign FC-AGYW dyads to treatment arm (IMARA-SA *n* = 263 or HP *n* = 262) following the baseline assessment. The AGYW will select a colored paper from a hat that determines the family’s group assignment. Assessors but not intervention staff will be blinded to treatment arm at 6- and 12-month follow-up.

### Training interventionists (IMARA-SA and health promotion)

Training for both conditions will last approximately 30 h, and we will train IMARA-SA and HP interventionists separately. Interventionists will review their assigned curriculum and related training manuals. Training for both programs will stress the importance of following the manualized protocol to ensure fidelity across interventionists and of completing fidelity measurements at the end of each workshop day. Following review of the curriculum, interventionists will practice delivering each activity, taking turns serving as group leaders and participants. Each interventionist will be “certified” as competent to deliver IMARA-SA or the HP program by the site Principal Investigator and study sub-investigator. Refresher trainings will occur annually and as needed if observer fidelity ratings indicate drift and non-compliance.

### Supervision, quality assurance, and treatment Fidelity

We will use a detailed manual and facilitator guide, conduct weekly supervision, and assess fidelity using facilitator self-report and observer ratings of adherence and competence (see below). Adherence measures will determine if the program was delivered as intended (yes/no), and competence ratings will indicate the quality of delivery. During ongoing supervision, a trained member of the study team will review fidelity reports, discuss session activities, problem-solve difficulties, and provide interventionists with feedback. If interventionists deviate from the curriculum, the supervisor will provide additional training until fidelity is achieved.

### Intervention delivery

Interventionists will be South African, female, and Black or mixed race to match AGYW and FC. Both interventions will be delivered over two sessions (about 10 h of content). We will enroll approximately 16 dyads per cohort, and we will enroll two cohorts every 6 weeks over 24 months. We will provide breakfast and lunch on both days. All intervention activities will occur at research sites in Klipfontein/Mitchells Plain.

#### Description of the interventions: Informed Motivated Aware and Responsible Adolescents and adults- South Africa (IMARA-SA)

The IMARA curriculum was subject to a comprehensive and systematic adaptation process prior to this RCT. The details of the adaptation process are presented elsewhere [81]. Separate FC and AGYW groups will run simultaneously, cover parallel content, and address individual, social, and structural drivers of HIV-risk (Table 1). Joint activities are designed to enhance FC credibility as a resource for HIV/STI prevention and facilitate practice of new communication skills. Additional activities will address conflict negotiation, assertive communication, and strengthening the AGYW-FC relationship. Interventionists will use interactive and experiential activities to address key constructs. The group format promotes structural change by building community norms for prevention (e.g., HTC and PrEP uptake) and reducing HIV stigma. IMARA-SA’s goals and motto emphasize strong FC-AGYW relationships, sisterhood, empowerment, and motivation for HIV/STI prevention, and build group cohesion. FC and AGYW will sign a pact to confirm commitment to the program. At the end of session 1, participants will receive homework to complete for session 2. Woven throughout IMARA-SA is the impact of mental health, gender-based violence, and alcohol and drug use on HIV-risk.

**Table 1 Tab1:** IMARA-SA Curriculum

Theory	Selected IMARA-SA Activities
Individual Factors	
Knowledge, attitudes, beliefs, skills about HIV, STI, PrEP, HTC	Facts of HIV/AIDS/STI/PrEP/HTC; Prevalence for adolescent girls and young women; PrEP education video; Perceived vulnerability; Personal risk triggers (e.g., people, places, feelings) and risk plans; Demonstrate and practice condom use; De-mystifying HIV testing; Importance of regular HTC and PrEP where appropriate to risk behavior.
Mental health	Destigmatize mental health; Links between mental health problems and HIV-risk behavior; Recognize how feelings trigger risk taking; Teach healthy coping strategies; Recognize the value of the body; Substance use and risk taking; Referrals for counseling
Social Factors	
Family context Geographically constrained networks	Importance of strong FC-AGYW relationships, open and positive communication, and FC monitoring for AGYW mental health and reduced HIV/STI-risk; FC-AGYW warmth and positive interactions; Create personalized monitoring plans; Teach and practice effective communication with FC and family; Discuss risk in the context of neighborhood and sexual networks.
Structural Factors	
Gender dynamics Partner relationships HIV/AIDS stigma & discrimination	Expectations of women; Media images; Healthy and unhealthy relationships; intimate partner violence; Gender-role expectations and stereotypes; Impact of gender dynamics on HIV/STI risk; Implications of age discrepant partners and concurrent partnerships (e.g., the added importance of HTC and PrEP); Assertive communication with partners and peers; Changes in community norms to reduce stigma toward HIV/AIDS, PrEP, and HTC.

### Time- and attention-matched control: general health promotion

The HP control group is a time-matched family-based intervention previously delivered to families in SA and translated into Xhosa. The program promotes healthy living by encouraging good nutrition, exercise, and violence reduction (Table 2). Similar approaches will be used by interventionists, including interactive games, videos, worksheets, and group discussion. Like IMARA-SA, FC and AGYW will meet in separate groups and together to review material and learn about nutrition, substance use, exercise, and other relevant health topics. HIV/AIDS prevention is addressed briefly given the high prevalence in SA.

**Table 2 Tab2:** Health promotion topics

Topics	Selected Activities
Media Literacy	Media influences on body image, weight, beauty; Obesity epidemic in SA and the role of the media (e.g., digital altering, manipulation)
Healthy Eating	Healthy eating; impact of fast food; Nutrition labels; Meal logs to track food choices
Violence	Types and prevalence of violence (gang, domestic, bullying, dating); Links between violence and health; Impact of families and communities; Tips to prevent violence.
Alcohol/Drugs	Prevalence of drug and alcohol use among teens; Impact of drugs and alcohol on the brain; Costs of drug/alcohol use on families and communities; Resources for counseling
Physical Activity	Impact of media and technology on physical activity (e.g., time spent on TV, phones); Benefits of exercise and relation to overall health and well-being; Practice and planning for one physical activity per day.

#### Contamination

We will minimize contamination across arms as follows. (1) Interventionists will not overlap, and training will occur separately. (2) Treatment conditions will occupy separate floors at the site to reduce participant contact. (3) We will assess exposure to IMARA-SA among control participants at 6- and 12-months. (4) We will adjust for exposure in the data analyses.

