#### Mediators and moderators

We will assess HIV/STI knowledge, attitudes, beliefs, and skills, [86–88] mental health, trauma, and intimate partner violence exposure, [89–92] PrEP knowledge and attitudes, quality and quantity of FC-AGYW communication, [32, 93, 94] parental monitoring, [95] and warmth and closeness in the relationship, [96] gender dynamics and partner communication, [94, 97–99], HIV/AIDS and PrEP stigma, [100], peer influence, [82] and substance use [82]. At 6- and 12-month follow-up, control group participants will indicate if they heard about IMARA-SA (yes/no) and what they heard (open-ended) to assess contamination.

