### Statistical analysis

We will generate frequencies and summary statistics of predictor and outcome variables to screen and clean the data. We will evaluate randomization by comparing intervention groups on baseline variables using chi-square tests for categorical variables and t-tests or nonparametric Wilcoxon rank-sum tests for continuous variables. In subsequent analyses, we will adjust for predictor variables on which baseline randomization is not successful. We will examine if AGYW who complete the 6- and 12-month assessments differ systematically on baseline data from those lost to follow-up. We will examine correlations among the variables, inspect scale reliabilities to create appropriate scales, and create summary scores as appropriate (e.g., mental health problems). We will use models with random intercepts to account for clustering (if needed) and test the significance of clustering of subjects within groups.

We will analyze binary outcomes using logistic regression and continuous outcomes using linear regression. We will test the effect of the intervention on the primary and secondary outcomes and theoretical mediators, adjusting for confounders and the outcome at baseline as additional independent variables. Analyses combining time points will use generalized linear mixed-models with subject-specific random effects to account for correlation within repeated measurements. We will test an average effect across time points and effects on patterns of change from 6- to 12-months using interactions with time. Survival analysis methods will assess the effect of the intervention on incident STIs, using extended Cox regression models with fixed and time-varying covariates to estimate univariable and multivariable hazard ratios for associations of exposures with incident STI. Treatment effects may differ systematically depending on various factors, such mental health or substance use. We will test mediator and moderator effects according to Baron & Kenny [101] and Cohen & Cohen [102]. We will include interactions between treatment condition and covariates in the GLM, and obtain estimates for regression coefficients of the interaction terms, 95% confidence intervals, and *p*-values for the hypothesis tests.

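### The unrestricted commitment to adjust for IMARA-SA exposure, a post-randomization self-report taken only from controls, can replace the randomized comparison with one against self-selected unexposed controls

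*Protocol article*

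**What the plan says.** The Contamination section lists four measures. The first two are design steps: separate interventionists and training, and separate floors. The third is measurement: "We will assess exposure to IMARA-SA among control participants at 6- and 12-months". The fourth is analytic: "We will adjust for exposure in the data analyses". It names no outcome or model, and does not say whether the adjusted analysis is primary or supplementary.

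The Mediators and moderators section gives the instrument: "control group participants will indicate if they heard about IMARA-SA (yes/no) and what they heard (open-ended) to assess contamination". The 6- and 12-month visits are also when the primary and secondary outcomes are measured.

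The Statistical analysis section sets the models: "We will analyze binary outcomes using logistic regression and continuous outcomes using linear regression". Treatment effects are estimated "adjusting for confounders and the outcome at baseline as additional independent variables". IMARA-SA exposure is not mentioned there. No section names an as-randomized analysis without the exposure term as primary.

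**The concern.** A covariate can be added safely to a treatment-effect model when it is fixed before randomization. Exposure as defined here arises after randomization, is reported by the participant, and is undefined in one arm. Conditioning on it splits the control arm by a characteristic that has no counterpart in the IMARA-SA arm.

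Controls who hear of the program may differ from those who do not. The article recruits partly by word of mouth and clinic contact in densely populated townships, so hearing of IMARA-SA could go with social ties or clinic contact. These could also relate to STI, HTC and PrEP uptake. If so, the adjusted contrast mixes the intervention effect with that selection, and an effect can appear, or be hidden, without any change in what the intervention does. Because the commitment is general, all three primary outcomes could be affected.

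**Working it through.** **Inputs from the article.** Allocation is 1:1 with 525 dyads (Randomization). The test is two-sided at alpha 0.05, with 80% retention and a 20% control proportion as one planning case (Sample size calculation). This gives 525 × 0.80 / 2 = 210 per arm.

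**Assumed, because the article does not give them.** *c* is the share of controls reporting exposure. *r* is the risk in exposed controls divided by the risk in unexposed controls.

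**Step 1: what the coefficient estimates.** Write logit P(Y) = a + bT + gE, with T = 1 for IMARA-SA and E = 1 for an exposed control. With E = 0 throughout the IMARA-SA arm, there are three groups and three parameters:

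- unexposed controls: a
- exposed controls: a + g
- IMARA-SA: a + b

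So b is exactly the log odds ratio of IMARA-SA against unexposed controls, and exposed controls affect only g. With further covariates it is the same contrast conditional on them. Fits to simulated data (400,000 participants) agreed to three decimals in every scenario.

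**Step 2: other codings.** With E = 1 in the IMARA-SA arm, the treatment term compares IMARA-SA with exposed controls only. With E missing there, a complete-case model drops that arm. Neither restores the randomized contrast.

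**Step 3: size under a true null.** Risk is 0.20 in both arms and exposure itself has no effect. The control arm must average 0.20, so the unexposed-control risk is

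u = 0.20 / (1 − c + c·r), and the apparent RR = 0.20 / u = 1 − c(1 − r).

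The rejection probability is Φ(δ − 1.96) + Φ(−δ − 1.96), with δ = |0.20 − u| / √[0.20 × 0.80/210 + u(1 − u)/(210(1 − c))].

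Worked case, c = 0.20 and r = 0.5: u = 0.20/0.90 = 0.222; RR = 0.90; OR = (0.20/0.80)/(0.222/0.778) = 0.875; δ = 0.0222/0.0423 = 0.525; rejection probability = 0.082.

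| r | c | u | apparent RR | type I error |
|---|---|---|---|---|
| 1 (unrelated to risk) | any | 0.200 | 1.00 | 5.0% |
| 0.75 | 20% | 0.211 | 0.95 | 5.7% |
| 0.75 | 30% | 0.216 | 0.925 | 6.6% |
| 0.5 | 5% | 0.205 | 0.975 | 5.2% |
| 0.5 | 10% | 0.211 | 0.95 | 5.8% |
| 0.5 | 20% | 0.222 | 0.90 | 8.2% |
| 0.5 | 30% | 0.235 | 0.85 | 12.4% |
| 1.5 | 20% | 0.182 | 1.10 | 7.3% |
| 1.5 | 30% | 0.174 | 1.15 | 9.6% |

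**Step 4: a second set of assumptions.** Half the AGYW were given 30% risk and half 10%, with 210 per arm and 4,000 simulated trials per scenario. Exposure of 30% in one risk group and 10% in the other gave a null OR of 1.09 (more exposure at high risk) or 0.94 (more at low risk), with type I error of 5.7% to 5.8%. A 50%/10% split gave 8.9% to 10.2%. The as-randomized analysis of the same trials gave 4.4% to 5.0% throughout.

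**The case against.** The strongest reply is that the fourth contamination measure is one unspecific sentence. The Statistical analysis section, which does specify the effect model, lists other covariates and omits exposure. A full analysis plan may place the adjustment in a sensitivity analysis, and coding exposure as 0 in the IMARA-SA arm is an assumption. This stands in part: a reader might infer that the headline estimate is certain to be exposure-adjusted, and the article does not establish that. What it does contain is a stated, unlimited commitment to adjust, and no coding of a control-only covariate recovers the randomized contrast. A plan that followed the sentence literally would build in the problem.

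Second, the bias may be trivial. This also stands. The exposed share and its relation to risk are not given, the design steps are meant to keep contamination low, and adjustment for confounders and the baseline outcome could absorb some selection. Near-nominal error is as consistent with the article as 12%.

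Third, a reader might extend the point to the survival analysis, where incident STI is modelled "using extended Cox regression models with fixed and time-varying covariates". The article does not support that. It names no time-varying covariate, so nothing shows that post-randomization behavior would be conditioned on. The same sentence also refers to associations of exposures with incident STI, so at least part of it may be associational.

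**Conclusion.** The point holds in a limited form. As written, the commitment permits an exposure-adjusted analysis as the main one. With exposure entered as a covariate set to 0 in the IMARA-SA arm, the treatment coefficient is exactly IMARA-SA versus controls who say they had not heard of it. That follows from the algebra and does not depend on the illustrative figures.

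The consequence for the estimate does depend on them. Bias ranges from none, when exposure is unrelated to risk and has no effect of its own, to an apparent RR of 0.85 with 12% type I error, or 1.15 in the other direction, at the extremes examined. Even with no bias, the contrast is not the one that was randomized.

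A reader might also conclude that a complier-average estimate with randomization as the instrument would settle the matter. The data described do not support that: having heard about a program is not receipt of a 10-hour workshop, so treating the item as treatment receipt would misstate the complier effect.

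**What to change.** Replace the fourth contamination measure with a statement that all primary and secondary outcomes are analyzed as randomized, with no exposure term in the effect model. Report the proportion of controls who had heard of IMARA-SA descriptively at 6 and 12 months, with a summary of what they heard; as the item is planned, only the control arm supplies this figure. Put any exposure-adjusted or contamination-corrected estimate in a labelled sensitivity analysis, state its assumptions, and note that the item records awareness of the program, not receipt of it.

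The cost is about one sentence and no new data. The downside is that the as-randomized estimate is attenuated if contamination is real. For example, take a true RR of 0.65 and 20% of controls exposed, unrelated to baseline risk, with exposure cutting their risk by a fifth. The control risk falls to 0.20 × (0.80 + 0.20 × 0.80) = 0.192, and the as-randomized RR becomes 0.13/0.192 = 0.68. The descriptive report and the sensitivity analysis are the place to discuss that.

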### Study assessments

AGYW and FC will complete 3-h baseline, 6-, and 12-month follow-up assessments, including STI testing and HTC. Surveys will be completed via ACASI. To facilitate retention, we will obtain extensive contact information for participants and three additional individuals who will always know how to reach them.

#### Primary outcomes

At 6-month follow-up, we will examine AGYW STI incidence (gonorrhea, chlamydia, and trichomoniasis), PrEP uptake and 1-month supply of medication, and HTC uptake.

Secondary Outcomes: At 12-month follow-up, we will examine AGYW STI incidence (gonorrhea, chlamydia, and trichomoniasis), PrEP prescription and 1-month supply of medication, and HTC uptake. At 6- and 12-month follow-up, we will assess AGYW sexual behavior (e.g., condom use, substance use during sex, number of partners, concurrent partners), using the AIDS Risk Behavior Assessment, [82] HIV incidence via HTC, and self-reported adherence to ART and PrEP (where appropriate) using Wilson’s 3-item scale [83]. We will use standard cost evaluation methods [84, 85] to assess IMARA-SA’s costs, including personnel time and non-personnel resources (e.g., travel expenses, snacks, incentives, curricular materials).

#### Mediators and moderators

We will assess HIV/STI knowledge, attitudes, beliefs, and skills, [86–88] mental health, trauma, and intimate partner violence exposure, [89–92] PrEP knowledge and attitudes, quality and quantity of FC-AGYW communication, [32, 93, 94] parental monitoring, [95] and warmth and closeness in the relationship, [96] gender dynamics and partner communication, [94, 97–99], HIV/AIDS and PrEP stigma, [100], peer influence, [82] and substance use [82]. At 6- and 12-month follow-up, control group participants will indicate if they heard about IMARA-SA (yes/no) and what they heard (open-ended) to assess contamination.

### Retention

We will collect participant contact information at baseline and the contact information for at least three individuals (i.e., collaterals) who will “always know where they are.” We will contact individuals monthly to update our information. We will use multiple methods, including text, email, or phone to reach them. One month before their 6- and 12-month follow-up, we will remind them of their next scheduled visit. For AGYW or FC whom we cannot reach, we will visit their homes and contact their collaterals for assistance. We will continue to seek them until the window for their assessment has closed.

Timeline

**Table Taba:** 

Study Activities	Year 1				Year 2				Year 3			
Quarter	1	2	3	4	1	2	3	4	1	2	3	4
Preparation of tools/procedures, IRB approval	X	X										
Staff recruitment and training		X										
Baseline assessments and intervention delivery			X	X	X	X						
6-month follow-up assessments					X	X	X	X				
12-month follow-up assessments							X	X	X	X		
Data analyses, write-up, and results dissemination									X	X	X	X

### Data management

Each participant will be assigned a unique identification (ID) number, which will be used for survey and laboratory data. Most survey data will be collected using Qualtrics, a web-based platform maintained by the University of Illinois at Chicago (UIC). Data that are collected using paper forms will be double entered for accuracy. All paper data will be kept in locked cabinets at the research site. Data will be stored in password-protected cloud-based systems and secure servers maintained by UIC and DTHF. Laboratory data will be collected by trained clinic staff and recorded in participant case report forms, which will be stored under lock and key at the research site and routinely transcribed into an electronic spreadsheet. Data will be accessible only to study personnel. Co-PIs will review all external requests to use the data, and data files provided to individuals will be stripped of identifiers. Study investigators will check for the completeness and accuracy of data, and confidentiality of records will be upheld.

### Statistical analysis

We will generate frequencies and summary statistics of predictor and outcome variables to screen and clean the data. We will evaluate randomization by comparing intervention groups on baseline variables using chi-square tests for categorical variables and t-tests or nonparametric Wilcoxon rank-sum tests for continuous variables. In subsequent analyses, we will adjust for predictor variables on which baseline randomization is not successful. We will examine if AGYW who complete the 6- and 12-month assessments differ systematically on baseline data from those lost to follow-up. We will examine correlations among the variables, inspect scale reliabilities to create appropriate scales, and create summary scores as appropriate (e.g., mental health problems). We will use models with random intercepts to account for clustering (if needed) and test the significance of clustering of subjects within groups.

We will analyze binary outcomes using logistic regression and continuous outcomes using linear regression. We will test the effect of the intervention on the primary and secondary outcomes and theoretical mediators, adjusting for confounders and the outcome at baseline as additional independent variables. Analyses combining time points will use generalized linear mixed-models with subject-specific random effects to account for correlation within repeated measurements. We will test an average effect across time points and effects on patterns of change from 6- to 12-months using interactions with time. Survival analysis methods will assess the effect of the intervention on incident STIs, using extended Cox regression models with fixed and time-varying covariates to estimate univariable and multivariable hazard ratios for associations of exposures with incident STI. Treatment effects may differ systematically depending on various factors, such mental health or substance use. We will test mediator and moderator effects according to Baron & Kenny [101] and Cohen & Cohen [102]. We will include interactions between treatment condition and covariates in the GLM, and obtain estimates for regression coefficients of the interaction terms, 95% confidence intervals, and *p*-values for the hypothesis tests.

We will evaluate the CE of IMARA-SA with respect to STI acquisition, the net cost of the intervention to the health system adjusting for cost savings from STI reduction, and explore HIV incidence where possible. We will conduct individual CE analyses for each STI (i.e., gonorrhea, chlamydia, and trichomoniasis) to compare the CE of IMARA-SA to interventions that focus on only one STI, as is typical in the limited published literature on STI prevention. The main CE analysis will include all 3 STIs and assess the overall CE of IMARA-SA. In addition, we will conduct two supplementary analyses to estimate: (a) the CE of IMARA-SA when viewed strictly as an HIV prevention intervention; and (b) the CE with all 4 STIs (gonorrhea, chlamydia, trichomoniasis, and HIV). Finally, we will assess the net cost to the health system from implementing IMARA-SA, adjusting for cost savings related to the reduction of STIs. The main outcome for the analyses is the CE ratio, defined as the incremental cost of the program per infection prevented by the intervention.

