### Identification and recruitment of participants

The study will take place in Phillippi and the surrounding townships including Nyanga, Gugulethu and Khayelitsha, located in the Cape Town metropolitan. These areas are densely populated, have a high HIV burden, and are poorly resourced. Recruitment strategies include street outreach, word-of-mouth referrals, flyers, and clinic-based contacts by study personnel. The majority of the residents are Black and mixed race. We will enroll AGYW and a FC, defined as an important and influential female in AGYW’s life (e.g., mother, aunt). AGYW will be: a) Black or mixed race; b) 15–19 years-old; c) residing in Phillipi and the surrounding areas who d) speak Xhosa, English, or a combination, as these are the primary regional languages. AGYW may or may not be sexually active, and information about AGYW sexual activity will not be shared with FC. FC will be: a) selected by the AGYW and agreed upon by the legal guardian; b) 24 years or older; c) living with or in daily contact with the AGYW; and d) a speaker of Xhosa and/or English. We will include HIV-infected and uninfected FC and AGYW, and AGYW or FC who become HIV+ and/or pregnant during the study may continue to participate. AGYW and FC must agree to participate as a dyad, but AGYW refusal will supersede FC consent. All participants, regardless of randomization status, will be followed for 12 months with visits conducted at 6 and 12-month intervals (Fig. 1).

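### Beyond the baseline outcome and unnamed confounders, covariates are chosen by baseline significance tests, which pick up chance differences rather than prognostic strength

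*Protocol article*

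**What the plan says.** All of the covariate rules stand in the Statistical analysis section of the protocol article.

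- **Baseline tests.** "We will evaluate randomization by comparing intervention groups on baseline variables using chi-square tests for categorical variables and t-tests or nonparametric Wilcoxon rank-sum tests". No significance level and no list of variables is given.
- **Their consequence.** In subsequent analyses "we will adjust for predictor variables on which baseline randomization is not successful".
- **Adjustment that needs no test.** Effects on the primary and secondary outcomes and the mediators are tested "adjusting for confounders and the outcome at baseline as additional independent variables". The confounders are not named.
- **Survival models.** Incident STI is also analysed "using extended Cox regression models with fixed and time-varying covariates". The covariates are not named.

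Two further statements matter. Under Randomization, allocation is 1:1 (263 and 262) after the baseline assessment: "The AGYW will select a colored paper from a hat that determines the family’s group assignment". The article describes no stratification. Under Identification and recruitment of participants, "AGYW may or may not be sexually active", so STI risk is likely to differ widely within the sample.

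**The concern.** Under proper random allocation every baseline difference between arms is a chance difference. A significant test therefore does not show that randomization failed, and it says nothing about whether the variable predicts the outcome. Two consequences follow.

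1. Covariates enter because they happen to differ between arms. A strong predictor that happens to balance has no claim under this rule, although adjusting for it would still gain power.
2. Part of the primary model is left to the drawn allocation. Two trials with the same design and population would report effects from different models.

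At stake are some power on the primary outcomes and a primary estimate whose covariate set is known in advance.

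**Working it through.** The plan gives no figure for this point, so there is none to reproduce. The checks below size the rule. Apart from the trial size, the 80% retention and the illustrative 20% event proportion, their inputs are assumptions.

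**1. How often the rule fires by chance.** Assume a 0.05 level (the article states alpha = .05 only for its power calculations) and k independent baseline variables (the number is not given). The expected number flagged is 0.05k, and the chance of at least one flag is 1 − 0.95^k.

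| k | Expected flags | Chance of at least one |
|---|---|---|
| 10 | 0.50 | 0.40 |
| 15 | 0.75 | 0.54 |
| 20 | 1.00 | 0.64 |
| 30 | 1.50 | 0.79 |

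Correlated variables would change these chances but not the expected number of flags.

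**2. What the rule costs.** Logistic models were simulated with 420 analysed (0.80 × 525), 15 independent baseline covariates of which one is prognostic, a binary baseline outcome with 30% prevalence, about 20% events in controls, a treatment odds ratio of 0.5, and 3,000 runs per setting. Covariates were flagged at two-sided 0.05.

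| Prognostic covariate, log-OR per SD | Baseline outcome, log-OR | Power: baseline outcome + flagged covariates | Power: baseline outcome + fixed prognostic covariate | Gain (points) |
|---|---|---|---|---|
| 0.5 | 0.5 | 0.695 | 0.709 | 1.4 |
| 0.5 | 1.2 | 0.668 | 0.680 | 1.2 |
| 1.0 | 0.5 | 0.615 | 0.672 | 5.7 |
| 1.0 | 1.2 | 0.601 | 0.660 | 5.9 |

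- The prognostic covariate was flagged in about 4% to 6% of runs, which is the test level and is unrelated to its strength.
- Adding only flagged covariates to a treatment-only model bought nothing: power went from 0.695 to 0.693, 0.650 to 0.649, 0.615 to 0.609 and 0.593 to 0.588.
- Type I error was 0.045 to 0.052 for the two models in the table. The Monte Carlo standard error is √(0.05 × 0.95 / 3000) = 0.004, so there is no sign of inflation.

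**3. Sexual activity as the example.** Let f be the share sexually active, with STI risk 20% overall and 2% in the inactive. The risk in the active is p = (0.20 − 0.02(1 − f)) / f, and the variance explained is R² = f(1 − f)(p − 0.02)² / (0.2 × 0.8).

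| f | p | R² | 1/(1 − R²) |
|---|---|---|---|
| 0.5 | 0.380 | 0.20 | 1.25 |
| 0.6 | 0.320 | 0.135 | 1.16 |
| 0.7 | 0.277 | 0.087 | 1.10 |

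Read alone, this suggests 10% to 25% more effective sample size. That figure is against no adjustment, on a linear scale. Baseline STI is already in the planned model and overlaps with sexual activity. With baseline STI included (assumed prevalence 30% to 40% in the active and 2% in the inactive, and a raised risk of repeat infection), the extra linear-scale gain falls to about 4% to 17%.

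In logistic simulation at 420 analysed (odds ratio 0.5, baseline STI 35% and 2%, odds ratio 2.5 for baseline STI), adding sexual activity raised power from 0.62 to 0.66, 0.64 to 0.67 and 0.66 to 0.68 as f went from 50% to 70%. If the inactive have 5% risk, the rise is 1 to 3 points; at 10% it is at most 1 point.

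**The case against.** **The test rule is not the only route into the model.** A reader might infer that chance differences are adjusted for in place of strong predictors, or that sexual activity can enter only if a test flags it. The article does not support either reading. The baseline outcome, often one of the strongest predictors, is always included, and the confounder clause carries no test, so it could admit sexual activity. This part of the objection stands and limits the point to the additional, test-driven covariates.

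**The choice uses no outcome data.** Selection needs only baseline data and allocation, so the list could be settled before any outcome is compared. A reader might infer that the model cannot be fixed before outcomes are seen, or that the result is biased. Neither follows, and type I error held in simulation. What remains is that the covariate set depends on the draw.

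**The precision argument is looser than it looks.** In logistic regression, adjustment does not shrink the standard error of the treatment log-odds ratio: at 50% active it rose from 0.289 to 0.304. The gain is in power, because the conditional effect is larger. This stands, so the size is given as power.

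**Covariate lists belong in a statistical analysis plan.** True, and the absence of a list here is not the complaint. The selection rule is stated in the article. A plan that follows it inherits the weakness, and one that departs from it contradicts the article.

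**Baseline checks may catch a failed procedure.** Allocation is drawn by hand, so a check on its conduct is reasonable. But covariate adjustment is not the remedy for a failed allocation, and a significant test is weak evidence of one.

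**Conclusion.** The point holds as stated in the heading. The article lets baseline tests between arms add covariates to the treatment-effect models. That selects on chance and not on prognosis, and it ties the primary model to the observed allocation.

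The harm is modest. Under the assumed inputs, fixing a prognostic covariate in advance is worth about 1 to 6 points of power over the planned rule, and possibly less than 1 point if inactive participants have 10% risk. No inflation of type I error was found. The 64% and 79% chances of at least one flag rest on an assumed 0.05 level and on 20 or 30 independent variables, none of which the article states. The 10% to 25% gain in effective sample size should not be used, because it ignores the baseline STI term already planned.

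The change should be made because it is cheap and removes a data-dependent choice, not because the trial's conclusions are otherwise at risk.

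**What to change.** Amend the Statistical analysis section, and align the statistical analysis plan with it, as follows.

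1. Report baseline characteristics by arm descriptively, and drop the baseline tests as a rule for choosing covariates.
2. Adjust every primary model, including the Cox model for incident STI, for a short set fixed in advance whatever the observed imbalance: the baseline outcome, kept as planned, plus for example age and baseline sexual activity.
3. Replace the open reference to confounders with that list.
4. Label any further adjustment, including for variables that look imbalanced, as a sensitivity analysis.

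The article names sexual behavior only as a 6- and 12-month outcome. However, the survey is also given at baseline, and adjusting secondary outcomes for their baseline values implies that it is recorded then. Confirm this before listing it.

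The cost is wording only, with no added participants, visits or measurements if baseline sexual activity is recorded as expected. The list should be fixed before any outcome is compared by arm.
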